## Methods

Findings from the individual studies will be reported according to the appropriate EQUATOR checklist [32, 33]. This protocol is reported according to the SPIRIT checklist [34], supplemented by relevant items from the CONSORT extension to pilot and feasibility trials [35]. The clinical study is registered in clinical trials (NCT04847271). Any important changes to the protocol will be amended in the registry and reported in the relevant publication. A brief structured summary of the clinical study in the format of a WHO trial registration data set is provided in Supplementary file 1.

### Study design

An overview of the research project and design of the different studies is outlined in Fig. 1. The project incorporates qualitative and quantitative research methods and comprises four studies to be performed over 4 years, divided into two phases. The design, including combining feasibility with outcome evaluation, follows guidance from the Medical Research Council on assessing feasibility and evaluating complex interventions [36]. It is consistent with a hybrid type-1 approach, in which a clinical intervention will be tested while concurrently evaluating the implementation process by gathering information on its delivery and potential for implementation in a real-world situation [37]. Both implementation process outcomes and clinical outcomes will be assessed. In phase 1, two studies target healthcare professionals and managers in paediatric health care. Study 1 investigates implementation determinants among staff and managers at paediatric clinics in a cross-sectional, web-based survey. Study 2 builds on the implementation determinants identified in the survey and further explores them in a subsample of this population, using focus group discussions. Findings from these two studies will feed into an adaptation of PAP and provide input for an implementation strategy for phase 2 of the project. This second phase includes a clinical intervention in which the adapted PAP intervention is tested using a single-group before-after design (study 3) and a qualitative interview study (study 4). The clinical intervention will be evaluated using a single-group design in which children and one of their parents/guardians will take part in a PAP intervention for 4 months. Clinical outcomes in children and parents will be assessed after the intervention, with long-term follow-ups at 8 and 12 months after baseline. Pre- to post-intervention changes in implementation outcomes will also be measured using the same questionnaire as in study 1, with follow-up 12 months after baseline. Process outcome data will be collected during and after the intervention. Finally, a qualitative interview study (study 4) will explore experiences of PAP treatment among children with obesity and their parents/guardians. A reference group that includes children, parents/guardians, healthcare professionals, managers, and other stakeholders will be consulted throughout the project.

**Fig. 1 Fig1:**
[figure not shown]
Overview of project and design of the included studies

### Theoretical framework

Health care and healthcare systems have a high degree of complexity [38], involving a multitude of perspectives, structures, and stakeholders and making it a particularly challenging context in which to implement new interventions and other practices. Promoting and prescribing physical activity to children with obesity are a complex healthcare intervention, embedded by social processes surrounding the child that may involve their family, friends, the school, community, sports arenas/clubs, and the healthcare system. When studying and implementing a complex intervention in a complex context such as health care, as in this project, the use of a theoretical framework may facilitate implementation and increase the chances for its success [26, 39]. A theoretical framework for implementation that can explain social processes related to the necessary change of the childs’ behaviour is appropriate.

The Normalization Process Theory (NPT) was developed to understand and explain the social processes that frame the implementation of complex interventions in health care [38]. This theory is particularly suitable for feasibility studies of complex interventions in complex contexts, such as health care [40]. The NPT posits that implementation is a dynamic process, involving all those who carry out the implementation: healthcare professionals, organisational leaders, and patients and their families [41]. The theory is concerned with explaining what people *do* rather than their attitudes, beliefs, or perceptions and comprises 4 core constructs: coherence (sense making), cognitive participation (engagement), collective action (working/operationalising the intervention), and reflexive monitoring (evaluation). These constructs, which drive the implementation process, represent ways of thinking about implementation and focus on how interventions can become part of everyday practice [40].

In this project, the NPT was used in the planning of the project and will be used both as a framework for the qualitative studies and as a support for the clinical study in which we will examine implementation outcomes using an NPT-based instrument. Data collection, analysis, and reporting of findings will be guided by the NPT.

### Setting

The empirical arena of this research is the paediatric healthcare organisation in Region Västra Götaland, as well as the PAP clinics in Gothenburg. The paediatric healthcare organisation comprises seven specialist paediatric clinics in the city of Gothenburg, six clinics in surrounding communities, and 13 clinics in the remaining part of Region Västra Götaland. Approximately, 240 healthcare professionals (paediatric nurses, paediatricians, psychologists, dieticians, and physiotherapists) are involved in the treatment of children with obesity. For the clinical intervention, clinics in Gothenburg and surrounding communities will be invited to participate.

### The PAP intervention

The intervention that is to be adapted and evaluated in the clinical intervention (study 3) comprises PAP according to standardised procedures and, if needed, additional support provided by the PAP clinics. The PAP intervention itself consists of 3 core elements: a person-centred counselling dialogue, individually tailored physical activity recommendations with a written prescription, and individualised, structured follow-up (13). The initial dialogue is based on motivational interviewing [42], which has shown promising results in the treatment of paediatric obesity [43–45]. This counselling technique incorporates discussion about the patient’s self-efficacy beliefs and motivation for physical activity, known mediators of physical activity behaviour change [46–48].

The prescription includes recommendations for one or several types of physical activity that can be individual or group based and carried out in different settings, e.g. home, school, gym, or outdoors. Frequency, duration, and intensity of the chosen physical activity are specified. Available group activities are typically arranged by private or municipal associations.

In study 3, included children and parents/guardians will participate in an adapted PAP intervention during 4 months. The study period will be spread out over a calendar year, which will allow for seasonal variation in the activities provided and a mix of indoors and outdoors physical activity. At the end of the 4-month intervention, the participants will be encouraged to continue with their chosen activity or try another activity of their choice. To support implementation and facilitate sustainability, the intervention will be aligned with current standard care processes, existing infrastructure will be used, and the intervention will predominantly be carried out by regular staff at the paediatric clinics.

### Adaptation and implementation

Adaptation of PAP to the target group and the context will be performed in collaboration with the Centre for Physical Activity (CFFA) Gothenburg and representatives from paediatric health care, based on the findings from studies 1 and 2 and with input from the reference group. Adaptation is defined as a systematically planned and proactive process of modification aiming to fit the intervention into a new context and enhance its acceptability [47, 49]. The 2019 systematic review by Movsisyan et al. [49] will be used as guidance for the adaptation, considering the specific needs of the population and the circumstances of the paediatric healthcare organisation and assuring intervention salience and fit with the new context. The implementation determinants identified in study 1 and study 2 will be addressed in the PAP adaptation.

The identified implementation determinants also will provide input to the development of a tailored implementation strategy for those units who choose to participate in the clinical intervention. To support implementation of the adapted PAP intervention, information/education material will be developed. Relevant healthcare professionals will be offered education on the effects of physical activity, concept and components of PAP, and how to organise the structure of PAP routines on a local basis. Other educational needs identified in the survey and focus groups will also be addressed. A register of locally available physical activity service providers, e.g. sports associations, will be developed.

### Recruitment of study participants and sample size

For the assessment of implementation determinants in study 1, comprising a cross-sectional survey, all approximately 240 healthcare professionals and managers involved in the treatment of children with obesity at the different paediatric healthcare clinics in Region Västra Götaland will be invited to participate.

For study 2, comprising focus groups, we plan to recruit approximately 30 healthcare professionals of various disciplines who have experience from treating children with obesity and have some experience of using PAP. They will be recruited from paediatric clinics in Gothenburg and surrounding communities. Eligible healthcare professionals are paediatric nurses, assistant nurses, paediatricians, psychologists, dieticians, and physiotherapists. In addition, 6–10 first-line managers, senior managers, and development managers from the paediatric organisation will be recruited. A purposive sampling strategy will be used to select eligible participants.

For the assessment of clinical outcomes in study 3, we aim to recruit approximately 60 children with obesity who have been prescribed PAP and one of their parents/guardians from the paediatric clinics in Gothenburg and surrounding communities who agree to participate. Because this is a feasibility study, we have not undertaken a formal sample size calculation but aim to include a sufficient number of participants to provide information about practicalities such as recruitment and attrition rates, intervention fidelity, dose, and adherence, as well as for statistical analyses of clinical outcomes. We have also given consideration to the likelihood of a fairly large attrition rate at each time point. Uncertainties about the recruitment procedure, the capacity to achieve an appropriate sample size, and the intervention itself will be considered in terms of feasibility and whether it is of value to proceed to full-scale evaluation. Children and parents will be screened for eligibility by the staff at the participating paediatric clinics in conjunction with their first visit. All who meet the inclusion criteria will be given oral and written information about the study and asked about interest in participating. Inclusion criteria are as follows: being aged 6–12 years, diagnosed with obesity (BMI > ISO-BMI 30), having an insufficient physical activity level according to national recommendations, and having a parent who is willing to participate. Insufficient physical activity level is defined as not reaching the national guidelines recommendation of 60 min of moderate to vigorous physical activity per day [12]. Exclusion criteria are as follows severe psychiatric comorbidity, severe intellectual or physical disability, or planning to relocate outside the study area within 12 months. To support recruitment and reach the desired sample size, site coordinators will be appointed, trained, and provided with adequate study material.

For study 4, we expect to recruit approximately 10–15 children-parent pairs. Sample size cannot be determined in advance because data collection should ideally go on until no new information emerges in the interviews. Eligible children and parents/guardians will be identified in collaboration with staff at the involved clinics. A purposive sampling strategy will be used, aiming for maximum variation in gender, age, parent’s gender, age, and education. Inclusion criteria will include being aged 6–12 years, diagnosed with obesity, having an insufficient physical activity level, and having a parent who is willing to participate. Parents will be approached and invited to participate by the project coordinator, who will provide oral and written information about the study and its aims and give the opportunity to ask questions.

### Patient involvement

Both users (healthcare professionals) and end users (parents of children with obesity) have been involved in the design and planning of the project. We will continue to solicit user input throughout the project. We are collaborating with the patient organisation HOBS (health independent of size). User representatives are included in the reference group. The reference group will be consulted on an as-needed basis (e.g. in the recruiting process, the adaptation of PAP, the development of the clinical intervention, and in developing intervention material). Children’s and parents’ views and experiences of PAP will be solicited in interviews (study 4), which will contribute to evaluation of the PAP intervention and its feasibility, and provide input to further development of the intervention.

### Data collection and outcomes

#### Implementation outcomes

Implementation outcomes will be measured pre-implementation, post-intervention, and at 12-months follow-up. Data will primarily be collected from healthcare professionals and managers through a web-based questionnaire comprising several validated instruments. Primary implementation outcomes are the four core constructs of the NPT: coherence, cognitive participation, collective action, and reflexive monitoring. They will be assessed using the Normalization MeAsure Development (NoMAD), which measures implementation from an NPT perspective and reflects the four constructs [50, 51]. The validated Swedish version S-NoMAD [52] is used in this project and has been adapted to fit children with obesity and address both healthcare professionals and managers. The S-NoMAD comprises 23 items, answered on 11-point or 5-point Likert-type scales.

Secondary implementation outcomes are the acceptability, appropriateness, and feasibility of implementing PAP in paediatric health care. Acceptability is defined as the perception among stakeholders that a given treatment, service, practice, or innovation is agreeable, palatable, or satisfactory; appropriateness is the perceived fit, relevance, or compatibility of the innovation or evidence-based practice for a given practice setting, provider, or consumer and/or perceived fit of the innovation to address a particular issue or problem; and feasibility is the extent to which a new treatment, or an innovation, can be successfully used or carried out within a given agency or setting [53]. These outcomes will be measured with the Acceptability of Intervention Measure (AIM), Intervention Appropriateness Measure (IAM), and Feasibility of Intervention Measure (FIM) [54], all validated instruments with the purpose of assessing the fit and match of a practice or intervention to a given context, targeting different criteria [54]. The three measures comprise 4 items each, answered on 5-point Likert-type scales. Before use, they were translated and cross-culturally adapted into Swedish and adapted to children with obesity, following established procedures including forward and backward translation and validating the translation using cognitive debriefing [55, 56]. The translation aimed to produce a language version with conceptual equivalence with the original and relevance to the new target culture and context.

Barriers and facilitators will be explored in two open-ended questions, in which the respondents will be given the opportunity to describe their experiences and thoughts regarding determinants for implementing PAP in their clinic, expressed in their own words. They will also be further explored in the focus group study.

Acceptability of the intervention from the child’s perspective will be measured with the Client Satisfaction Questionnaire (CSQ-8) [57], translated to Swedish and adapted to children and parents. Feasibility for the child to participate in PAP will also be examined by collecting process data on fees, equipment, and transport costs of the chosen physical activity, as well as travel time, time spent at the activity, and at assessments and other contacts during the intervention.

Additional implementation process outcomes will be assessed as follows: recruitment and attrition rates will be examined. When possible and if participants consent, reasons for dropout will be documented. Intervention fidelity (intervention delivery as intended) and dose (quantity of intervention) will be captured by monitoring intervention components delivered. Other simultaneous treatment, e.g. dietary recommendations, will be documented. Availability of local physical activities will be documented. Data regarding intervention adherence and participation in the chosen physical activities will be collected via analogue and/or digital activity diaries.

#### Clinical outcomes

All clinical outcomes will be measured pre- and post-intervention and at 8 and 12 months’ after baseline. The primary clinical outcome will be physical activity level, measured as minutes per day spent in moderate to vigorous physical activity (MVPA) and assessed using the Axivity accelerometer (Axivity AX3, Axivity Ltd., UK). Accelometry is the most commonly used method in clinical and epidemiological research for objective measurement of physical activity, is easy to use for the study participant and the researcher, and has a high sensitivity for detecting changes in physical activity (30). The accelerometer will be placed above the child’s and parent’s hip in an elastic belt and worn 24 h per day for seven consecutive days. In this position, the accelerometer can be used to assess physical activity at different intensities. The accelerometer recording is accompanied by an activity diary to determine bedtime, non-wear time, and sport activities. A strict protocol for data quality assurance (malfunction, spurious data, wear time, valid days) will be used. A project coordinator will provide the accelerometer to the participants together with oral and written instructions, support the participants if necessary, and collect the accelerometer after use. Measurement procedure, quality assurance, data processing, and analysis will be supported by an experienced team at the Center for Health and Performance [58].

Secondary clinical outcomes will be physical activity patterns (time spent in different types of activities and at different intensity levels, including sedentary time) measured with accelerometry; anthropometric measures, i.e. BMI; and waist circumference, collected from medical charts. Metabolic risk markers will be assessed via blood pressure measures and blood samples, including fasting plasma glucose, high- and low-density lipoprotein cholesterol, insulin resistance, and triglycerides. In addition, patient-reported health-related quality of life will be measured using KIDSCREEN-10 [59], and the child’s sleep will be measured using the Insomnia Severity Index (ISI) [60, 61]. Parents’ perception about their child’s sleep will be measured using the Pediatric Insomnia Severity Index (PISI) [62, 63]. The child’s self-efficacy for physical activity, and motivation for physical activity, will be measured with validated instruments adapted to children with obesity and parents and appropriately translated to Swedish [64–67]. Adverse events will be monitored and documented.

Demographic data on children will be collected at baseline, including age, gender, comorbidities, and country of birth. Data on participating parents/guardians include age, gender, BMI, comorbidities, country of birth, and education level.

To enable missing data analysis, demographic data will also be collected for those who decline participation, when possible.

#### Qualitative data

For study 2, data will be collected from healthcare professionals and managers using focus group methodology [68]. Semi-structured focus group discussions will be conducted, with groups comprising a mix of professions. Managers will form separate focus groups. The focus group methodology was chosen to stimulate discussion among the participants and capture collective interaction and experiences. The discussions will be facilitated by a moderator and an observer. Discussions will be recorded and transcribed verbatim. A discussion guide will be developed to ensure that adequate data responding to the research questions are collected, and that the four NPT constructs are covered in the discussions.

For study 4, data will be collected in individual, semi-structured interviews with children who have participated in the PAP intervention and one of their parents/guardians. A purposive sampling strategy will be used, aiming to ensure maximum variation in the sample (e.g. child gender and age, parent gender, age, education level, and country of birth). Data collection will continue until no new information seems to be forthcoming in the interviews. The interviews will be recorded and transcribed verbatim. An interview guide will be developed to ensure that adequate data responding to the research questions are collected.

### Data analysis

#### Implementation outcomes

Implementation outcome data will be analysed in two steps. First (in study 1, where the purpose of this survey is to assess healthcare providers’ perceptions of PAP treatment with the aim of identifying implementation barriers and facilitators), baseline (pre-intervention) data will be analysed descriptively using absolute and relative frequencies, as well as means and standard deviations. Differences between age groups, years’ of experience, and different professions will be analysed using chi-square tests We will do a subgroup analysis of respondents from the Gothenburg clinics in which PAP has already been implemented, including access to extra support from the PAP clinics. Second (in study 3), in the subset of the study 1 participants in which the intervention is carried out, we will perform longitudinal analysis of changes after participating in the intervention, using data from pre- and post-intervention, and follow-up at 12 months after baseline. Average change over time will be analysed across the three time points using mixed linear modelling, given the assumption that data are normally distributed. Analyses will be per protocol, and missing data will be handled with maximum likelihood estimation. The free text answers to the open-ended questions related to implementation determinants will be analysed using qualitative content analysis [69].

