### Aims

The overarching aim of this project is to evaluate the prerequisites, determinants, and feasibility of implementing PAP for children with obesity in paediatric health care. Quantitative studies will investigate implementation and clinical outcomes, while qualitative studies will explore implementation determinants among different stakeholders.

Specific study objectives are as follows:Study 1: To examine how healthcare professionals and managers perceive working with PAP for children with obesity in terms of coherence, cognitive participation, collective action, and reflexive monitoring and how they perceive acceptability, appropriateness, and feasibility of a PAP intervention and, furthermore, to explore barriers and facilitators for working with PAP for children with obesity.Study 2: To explore experiences, barriers, and facilitators for using PAP for children with obesity among healthcare professionals and managers.Study 3: To evaluate the feasibility and acceptability of a PAP intervention for children with obesity on implementation outcomes and clinical outcomes, with physical activity pattern being the primary clinical outcome variable.Study 4: To explore children’s and parents’ experiences of participating in a PAP intervention, with a focus on perceived barriers and facilitators for implementing PAP.

Specific research questions are presented in Table 1.

**Table 1 Tab1:** Research questions

*Study*	*Preliminary title*	*Research questions*
1	Working with PAP for children with obesity in paediatric health care — a cross-sectional survey	How do healthcare professionals and managers perceive working with PAP for children with obesity in terms of coherence, cognitive participation, collective action, and reflexive monitoring?
		How do healthcare professionals and managers perceive PAP for children with obesity in terms of acceptability, appropriateness, and feasibility of the intervention?
		Is there a difference in the above variables between healthcare units, age groups, or professions?
		What are the perceived barriers and facilitators for working with PAP for children with obesity?
2	Experiences among healthcare professionals and managers of using PAP for children with obesity — a focus group study	What are the experiences of healthcare professionals and managers in paediatric clinics of working with PAP for children with obesity?
		What barriers and facilitators do they perceive related to implementing PAP for children with obesity?

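### Study 1 asks whether scores differ between healthcare units, but the stated comparisons omit units, and the named chi-square test ignores the order of the Likert scales and loses power

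*Protocol article*

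**What the plan says.** The research question for Study 1 (Aims, Table 1) reads "Is there a difference in the above variables between healthcare units, age groups, or professions". The variables it refers to are the four NPT constructs, and acceptability, appropriateness and feasibility.

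Data collection and outcomes (Implementation outcomes) describes the scales: "The S-NoMAD comprises 23 items, answered on 11-point or 5-point Likert-type scales". For AIM, IAM and FIM: "The three measures comprise 4 items each, answered on 5-point Likert-type scales".

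Data analysis (Implementation outcomes) makes four statements about these data:

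- For the baseline summary, the survey data are to be "analysed descriptively using absolute and relative frequencies, as well as means and standard deviations".
- For group comparisons, the plan takes age group, then experience, "and different professions will be analysed using chi-square tests". Healthcare unit is not in that list.
- For clinics, one further step is given, without a stated contrast: "We will do a subgroup analysis of respondents from the Gothenburg clinics in which PAP has already been implemented".
- For the same instruments in Study 3, the plan turns to a linear model: "Average change over time will be analysed across the three time points using mixed linear modelling, given the assumption that data are normally distributed".

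**The concern.** There are two separate problems.

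First, the question and the analysis name different factors. Units are in the question but not among the factors tested. Experience is tested but is not in the question. The Gothenburg subgroup analysis touches on units, but it looks at one set of clinics and states no contrast with the others. The question about units, as worded, has no stated test.

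Second, the named test does not suit the outcomes. A Pearson chi-square treats the answers on a 5- or 11-point scale as unordered labels. It would give the same result if the categories were shuffled. The same paragraph summarises these data by means and standard deviations and later models them linearly, so the authors themselves treat them as ordered scores.

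At stake is whether the survey can detect differences between professions or units. Its findings feed the adaptation of PAP and the tailored implementation strategy for the participating clinics. A real difference that goes unseen cannot inform that tailoring.

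**Working it through.** The article gives no sample size, power or error rate for these comparisons, so there is no figure to reproduce.

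**Inputs from the article.** About 240 invited (Recruitment). Clinics: 7 + 6 + 13 = 26 (Setting). Five professions named in Setting. Scales of 5 and 11 points. Significance level 0.05, stated under clinical outcomes without sidedness.

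**Assumptions not in the article.** Equal group sizes; latent normal scores cut into equally likely categories; ordered group means spanning 0.5 SD; 240 respondents (full response) or 120 (50%); intraclass correlation (ICC) for clinic of 0.01 to 0.10.

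**Factors side by side.**

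| Factor | Question in Table 1 | Named test |
|---|---|---|
| Healthcare unit | yes | none (Gothenburg subgroup only) |
| Age group | yes | chi-square |
| Profession | yes | chi-square |
| Years of experience | no | chi-square |

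**Sparseness.** Average cell count = N / (groups × categories).

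- 5 professions × 5 points: 240/25 = 9.6; with 120 respondents, 120/25 = 4.8.
- 5 professions × 11 points: 240/55 = 4.4; with 120 respondents, 120/55 = 2.2.
- 26 clinics × 5 points: 240/130 = 1.8.

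In the simulated 5 × 11 table at N = 240, about 73% of expected counts were below 5.

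**Why power falls.** The chi-square test spends (groups − 1)(categories − 1) degrees of freedom: 4 × 4 = 16 for a 5 × 5 table and 4 × 10 = 40 for a 5 × 11 table. A Kruskal-Wallis test or one-way linear model spends 4 in both cases.

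**Simulated power (2,000 runs per setting, 0.5 SD span).**

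| Scale | Groups | N | Chi-square | Kruskal-Wallis |
|---|---|---|---|---|
| 5-point | 2 | 240 | 0.84 | 0.95 |
| 5-point | 3 | 240 | 0.51 | 0.76 |
| 5-point | 5 | 240 | 0.29 | 0.52 |
| 11-point | 2 | 240 | 0.70 | 0.97 |
| 11-point | 3 | 240 | 0.36 | 0.78 |
| 11-point | 5 | 240 | 0.18 | 0.54 |
| 5-point | 5 | 120 | 0.15 | 0.25 |
| 11-point | 5 | 120 | 0.10 | 0.27 |

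One-way analysis of variance was within about 0.01 of Kruskal-Wallis. A separate run of the two five-group settings at N = 240 gave 27% against 49% and 17% against 52%. With no true difference, chi-square rejected in about 4-5% of runs, so its error rate holds.

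**Clustering by clinic.** Respondents per clinic at full response: 240/26 = 9.2. For a contrast between clinics, the design effect is 1 + (9.23 − 1) × ICC, which gives 1.08, 1.41 and 1.82 for ICC 0.01, 0.05 and 0.10. Chi-square size was simulated with 26 clinics of 9 respondents and a 5-point item (3,000 runs):

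| Factor | ICC 0.05 | ICC 0.10 |
|---|---|---|
| Varies within clinics | 0.045 | 0.040 |
| Clinic-level, 7 against 19 clinics | 0.072 | 0.084 |

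Only the clinic-level contrast is inflated.

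**The case against.** The strongest reply is that this is a descriptive survey in a condensed article and that chi-square is a valid way to compare response frequencies, which the paragraph also plans to report. The text does not say what is cross-tabulated; it may be single items or collapsed categories. Adaptation also draws on the focus groups, the open-ended questions and the reference group, not on these p-values alone. The power figures rest on an assumed effect. With small differences, the better test also misses most of them: in one run with unequal professions and 170 respondents, a total spread of 0.4 SD gave about 9% power for chi-square and 23% for analysis of variance.

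Much of this stands, and it limits the severity. It does not remove the point. The test and the factors are stated, not left out, and the factors conflict with the article's own question. If chi-square is applied to items, it does not directly answer a question about constructs. If it is applied to scores, it needs a categorisation that the article does not give. In every setting with a true difference, the order-respecting test had the higher power.

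A reader might infer more than the text supports:

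- That clinics are ignored altogether. The Gothenburg subgroup analysis follows directly after the chi-square sentence.
- That a planned Gothenburg-against-rest comparison has intervals that are too narrow. No such comparison or interval is stated.
- That clustering undermines the tests by profession, age or experience. For a factor varying within clinics, the simulation shows no inflation.

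**Conclusion.** The point holds in two parts. Healthcare unit is in the stated research question but has no stated comparison, which follows from the text alone. The chi-square test is a poor choice for ordered outcomes: with five groups and 240 respondents it roughly halves the power on a 5-point item and cuts it to about a third on an 11-point item. Those sizes depend on the assumed 0.5 SD span, equal groups, uncollapsed scales and full response; at 50% response both tests are weak, and chi-square remains the weaker.

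It would be wrong to conclude that the planned tests are invalid. Chi-square kept its error rate; the fault is lost power and sparse tables. Clustering matters only once a clinic-level contrast is added, as the question on units requires. Severity is low to moderate, because Study 1 is largely descriptive and the clinical outcomes in Study 3 are not touched.

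**What to change.** 1. For the NPT construct scores and the AIM, IAM and FIM scores, replace chi-square with a linear model or a Kruskal-Wallis test. Use an ordinal model for single items. Keep chi-square for nominal variables.
2. Add healthcare unit to the comparisons, at least as Gothenburg clinics against the others, with a random intercept for clinic or standard errors clustered by clinic.
3. Align Table 1 and the analysis section on the factors, including years of experience.
4. If a clinic ICC is reported, give it with its interval and only as a supplement. It does not show which units differ, it leaves out the Gothenburg contrast if that is fitted as a fixed effect, and 26 small clinics estimate it poorly. In a simulation with 5-6 respondents per clinic and a true value of 0.05, estimates ran from about −0.07 to 0.19.

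The cost is slightly more analysis work and a distributional or proportional-odds assumption to check. No extra data are needed, provided responses can be linked to clinics, and mixed linear models are already planned for the same outcomes in Study 3.
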